Preliminary efficacy will be assessed by considering changes in couples’ outcomes A to D over time. For the immediate intervention arm, the differences in outcomes A to D will be observed between receipt of the intervention and subsequent follow-up assessments at 3 months and 6 months (n=30). For the waitlist arm, the differences in outcomes A to D will be observed between receipt of the intervention after the 3-month assessment and subsequent follow-up assessment at month 6 (n=30). As such, this study will be able to pool and combine data from the 30 couples from the immediate intervention arm with data from the 30 couples from the waitlist arm to observe changes in outcomes (ie, from A-D) over a 3-month time period (N=60). Furthermore, through this study, we will also be able to observe changes in couples’ outcomes (ie, from A-D) for a longer period of time (6 months) for the immediate intervention arm (n=30). Comparisons in couples’ outcomes A to D by trial arm (immediate arm vs waitlist arm) will occur between baseline and month 3. In summary, the design we chose for the proposed 6-month pilot RCT is advantageous for 3 reasons: (1) it will allow us to compare differences between immediate intervention and delayed intervention arms for 3 months; (2) it will allow us to make comparisons within the delayed arm from no intervention before to intervention after (months 3 to 6) the assessment; and (3) it will facilitate generating additional intervention data that can be pooled from the immediate and delayed intervention arms to obtain more robust estimates of intervention effect size to more accurately estimate sample size and power for an efficacy RCT in the future.

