Longitudinal analyses will also be conducted [52-54], specifically for outcome C, relationship functioning variables, to explore changes over time and whether these changes differ by arm and by couples’ HIV serostatus. Specifically, generalized linear mixed-effects models (GLMMs) with SAS PROC GLIMMIX will be used to analyze the longitudinal data for outcome C from all 3 time points: baseline, 3 months, and 6 months after randomization. The analysis will fit a GLMM with fixed effects for time, a term for the pilot arm (immediate intervention vs delayed), and an arm-by-time interaction term. The GLMM will include random effects for the intercept and couple cluster (to account for within-couple correlation over time). Model fitting statistics will be used to determine the suitability of more parsimonious (eg, autoregressive) correlation structures and nonlinear effects for time. From the fitted GLMMs, the primary hypothesis will be examined by testing whether the coefficient of the group-by-time interaction term (the difference in slopes between immediate intervention vs delayed) is different from 0. The primary analysis will be performed at the couple level, with exploratory analyses performed at the individual level. For individual-level analyses, all models will use similar GLMMs with random effects to account for the intracluster correlation of couple members. We will also explore outcomes (A-D) at the individual level (n=120) by looking at each participant’s changes over time as secondary analyses of interest using multilevel models.

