#### Power, Sample Size, and Effect Size Estimations

All power calculations were performed with PASS 2020 [59]. For the couple-level analyses, with 60 couples randomized to 2 arms (30 couples in each), for outcome C, we will have 80% power to detect a difference of 0.75 SDs of the mean relationship functioning measure (large effect [60]) using a linear model. For the dichotomous outcomes A and B, we will have 80% power to detect an absolute difference of 35% between the intervention and delayed conditions using a chi-square test. Our power increases for the outcomes analyzed at the individual level, where the correlation between individuals within a dyad must be considered (ie, the interdependence of individuals nested within dyads). For the incidence rate of outcome D assuming Poisson distribution, 30 couples in each arm will have 80% power to detect a difference of 50% rate reduction in STI rate (including HIV) between the intervention and delayed conditions at 6 months assuming a within-pair coefficient of variation between clusters at 0.25 and the intraclass correlation coefficient as high as 0.1 (even higher ICCs do not reduce rate reduction measure in a significant or meaningful way magnitude wise). For all analyses, the α level was set at .05 with 95% CI. This is a feasibility and acceptability trial that is only powered to detect large effects; however, if effect sizes are lower than hypothesized, we will use that information to properly power a large-scale RCT.

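### The time form in the outcome C primary model is chosen by fit on the trial's own data, so the quantity tested by the group-by-time coefficient is not fixed in advance

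*Protocol article*

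**What the plan says.** Under Primary Analyses, the outcome C model takes in baseline, month 3 and month 6, and it starts from time, arm and their interaction: "The analysis will fit a GLMM with fixed effects for time, a term for the pilot arm (immediate intervention vs delayed), and an arm-by-time interaction".

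A fit-based choice comes next: "Model fitting statistics will be used to determine the suitability of more parsimonious (eg, autoregressive) correlation structures and nonlinear effects for time". Only after that choice has been made does the section turn to inference, and it takes the test from the model so chosen: "From the fitted GLMMs, the primary hypothesis will be examined by testing whether the coefficient of the group-by-time interaction term" departs from zero. A parenthesis there describes this coefficient as the arm difference in slopes.

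No fit criterion, candidate set or time origin is named, and the text does not say whether a nonlinear time term would also be crossed with arm. The section on Aim 3 places the comparison of arms between baseline and month 3. The section on Randomization gives the delayed arm the intervention for the last 3 months. The power section sets the level: "For all analyses, the α level was set at .05 with 95% CI".

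**The concern.** A primary test should estimate one quantity that is fixed before the data are seen. Here the time form is picked from the data, and the coefficient with the same name is then read from whichever model won.

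A difference in slopes is a single number only while the arms differ by a straight line. Delayed access makes a bent arm difference plausible, because one arm starts the intervention at baseline and the other after month 3. At stake are what the outcome C result means and, under some versions of the unstated rule, whether the .05 level holds.

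**Working it through.** **Inputs from the protocol.** 30 couples per arm; three visits (baseline, month 3, month 6); α = .05, taken as two-sided because the test is for a difference from zero; couple-level primary analysis.

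**Assumptions.** Visit correlation 0.5 unless stated, SD 1, complete data, AIC or BIC as the fit rule, and the effect pattern in step 2. The protocol gives none of these.

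**1. The plan's own figure.** The power section says "we will have 80% power to detect a difference of 0.75 SDs of the mean relationship functioning measure". The normal approximation gives 0.75 × √(30/2) = 2.905, and Φ(2.905 − 1.96) = 82.8%. The two-sided t test gives 81.5%. The stated 80% is reproduced.

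**2. What the coefficient means under each form.** Let t = 0, 1, 2 in 3-month units. Suppose the effect d is complete after 3 months of access and lasts. The immediate arm gains (0, d, d), the delayed arm (0, 0, d), and the arm difference is (0, d, 0).

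- Linear time: slope = (month 6 − baseline)/2 = (0 − 0)/2 = **0**.
- Arm-specific quadratic from baseline: 2d·t − d·t² gives 0, d, 0 exactly, so the linear coefficient is **2d**.
- Time centred at month 3: the slope of that curve at t = 1 is 2d − 2d = 0. The coefficient then keeps its baseline-to-month-6 meaning in both forms.

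**3. Chance of rejection in this pattern.** The quadratic model's linear coefficient is −1.5·y₀ + 2·y₁ − 0.5·y₂. Its per-couple variance is (2.25 + 4 + 0.25)(1 − 0.5) = 3.25, so the SD is 1.803. For d = 0.75, (1.5/1.803) × √15 = 3.22, and Φ(3.22 − 1.96) ≈ 90%. Simulation (5,000 runs) gave:

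| True d | Linear time fixed | Common curvature only | AIC may pick arm-specific quadratic |
|---|---|---|---|
| 0.50 SD | 4.5% | 4.6% | 57% |
| 0.75 SD | 3.9% | 3.9% | 89% |

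In a further simulation (AIC, linear against arm-specific quadratic, correlations 0.5 and 0.7), the quadratic was chosen in 37-51%, 69-87% and 94-99% of runs for d = 0.3, 0.5 and 0.75. When chosen, its coefficient averaged 0.84-0.99, 1.07-1.21 and 1.50-1.56 SD per 3 months. When linear time was chosen, the coefficient was about 0.

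**4. Type I error with no arm effect** (20,000 runs per setting; common curvature none, mild or strong):

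| Rule | AIC | BIC |
|---|---|---|
| arm-by-time² a candidate, time from baseline, single coefficient tested | 8.5-9.2% | 6.1-8.4% |
| Same, but quadratic terms enter only as a pair | 4.9-8.1% | 5.0-6.6% |
| Joint 2-df interaction test when the quadratic is chosen | 7.3-7.6% | 6.0-7.3% |
| Only common time² may enter | 5.1-5.2% | 5.0-5.2% |
| Time centred at month 3 | 5.1-5.3% | 5.0-5.2% |

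With 37 couples per arm (74 enrolled, if split evenly) and mild curvature, the first row under AIC is 9.2%. Choosing only the correlation structure by AIC gave 4.9-5.5% (3,000 runs per setting).

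**5. A fixed alternative.** Categorical time with the baseline-to-month-3 arm contrast held 4.7-5.4%. For 0.75 SD at correlation 0.5, the unadjusted change has variance 2(1 − 0.5) = 1, so its power is that of step 1: 81.5% by the t test (82% simulated). Adjusting for baseline reduces the SD to √(1 − 0.25) = 0.866; then 0.75/0.866 × √15 = 3.354 and Φ(1.394) ≈ 92%, against 82.8% unadjusted by the same approximation.

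**The case against.** The strongest reply is that the plan speaks of nonlinear effects for time, separately from a single arm-by-time term, and describes that term as a difference in slopes. On that reading only common curvature enters, the coefficient keeps its meaning, and the level stays near 5%. This reading is fair, but the text does not exclude an arm-specific curve, and the same section asks whether changes over time differ by arm. Even on this reading, step 3 shows that the test misses an early effect that the delayed arm later matches. That loss comes from the crossover before month 6, not from the selection itself.

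It can also be said that this is a pilot powered only for large effects, that these analyses are introduced as exploring change, and that the criterion and candidates belong in a statistical analysis plan. That limits the consequence. Yet the section calls this its primary hypothesis, and an analysis plan that followed the stated rule would still let the data choose the primary coefficient.

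A reader might infer more than the documents support:

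- **That type I error simply rises to 8-10%.** It does not. The 20,000-run settings stay at or below about 9.2%, and most versions of the rule give less.
- **That choosing the correlation structure is part of the fault.** Its effect on the level is immaterial.
- **That the inflated coefficient would size the efficacy trial.** Aim 3 does speak of data to "obtain more robust estimates of intervention effect size to more accurately estimate sample size and power for an efficacy RCT in the future", but that sentence concerns intervention data pooled across both arms, not this coefficient.

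**Conclusion.** The point holds as one about an unfixed estimand. The rule lets fit decide the form of time in the model that supplies the outcome C primary test. If an arm-specific quadratic coded from baseline is among the options, the tested quantity switches between the baseline-to-month-6 slope difference and the difference in initial slope. With an effect complete by 3 months and full catch-up by month 6, these are about 0 and about 2d. Neither is the 3-month effect d that Aim 3 sets out to compare.

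The effect on the level is secondary and conditional: up to about 9% under the four conditions in the first row of the type I table, about 6-8% there with BIC, and near 5% with common curvature only or centred time. The criterion, candidate set, time coding, visit correlation and effect pattern are all assumed, because the protocol states none of them. The matter should be corrected, but no confirmatory decision rests on it in a pilot.

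**What to change.** Remove the fit-based choice of time form from the primary outcome C model. Specify in advance:

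- time as a three-level factor, with its arm interaction;
- unstructured covariance (six parameters for three visits) and small-sample degrees of freedom;
- one named test, the arm difference at month 3, adjusted for baseline or with baseline means constrained equal. This agrees with the comparison window already given under Aim 3.

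Keep linear and nonlinear time models, and any use of fit statistics, as labelled sensitivity analyses.

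The cost is a change of wording, with no new data. The choice of contrast does affect power, so it should be written out: left unadjusted for baseline, power is somewhat lower, about 81% at 0.75 SD with an assumed visit correlation of 0.5.

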### Randomization

An allocated randomization block of 2:2, via an embedded algorithm within the P3 DHI, will be used to randomly assign couples to one of the following 2 intervention conditions following the baseline assessment: (1) an immediate intervention condition where couples will be able to use the P3 DHI for 6 months or (2) a 3-month delayed intervention condition where couples will be able to use the P3 DHI for the last 3 months of the trial. For ethical reasons, a delayed control condition was chosen for the trial study to provide all couples with access to the intervention while also permitting the ability to compare outcome differences between trial arms for the first 3 months of the pilot RCT. In sum, all couples in the pilot RCT will have access to use the P3 DHI for a minimum of 3 months, which will enable data pooling of the entire couple sample (N=60; ie, first 3 months for the immediate intervention condition plus the last 3 months with the delayed intervention condition). The study design will also enable the examination of long-term effects of the P3 DHI (ie, effects after 6 months of use) on outcomes and their use of the P3 DHI among couples randomized to the immediate intervention condition (n=30). Randomization will be blinded to couples but not to the study staff (administrators).

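### Outcome C: the primary hypothesis tests a difference in slopes over baseline, month 3 and month 6, although the delayed arm also has P3 by month 6; this conflicts with the baseline-to-month-3 arm comparison set out under Aim 3

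*Protocol article*

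**What the plan says.** All references are to the protocol article.

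- **Primary Analyses.** The outcome C model uses data "from all 3 time points: baseline, 3 months, and 6 months after randomization", with "fixed effects for time, a term for the pilot arm (immediate intervention vs delayed), and an arm-by-time interaction term". The primary hypothesis is examined by "testing whether the coefficient of the group-by-time interaction term (the difference in slopes between immediate intervention vs delayed) is different from 0". There is no term for exposure that changes over time. On the shape of time, the text adds: "Model fitting statistics will be used to determine the suitability of more parsimonious (eg, autoregressive) correlation structures and nonlinear effects for time".
- **Randomization.** The control is "a 3-month delayed intervention condition where couples will be able to use the P3 DHI for the last 3 months of the trial". The immediate arm has access for all 6 months, so both arms have P3 by the month-6 visit.
- **Aim 3: Preliminary Efficacy of the Intervention.** Comparisons of "outcomes A to D by trial arm (immediate arm vs waitlist arm) will occur between baseline and month 3". The same section pools the first three months of access from both arms to estimate a single effect size.
- **Power, Sample Size, and Effect Size Estimations.** For outcome C with 30 couples per arm, "we will have 80% power to detect a difference of 0.75 SDs of the mean relationship functioning measure".

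**The concern.** The design gives one randomised comparison of P3 with no P3: the arms at month 3. The Aim 3 section says so, and the power section sizes outcome C for a two-group difference in means. The hypothesis test for outcome C is instead a single slope difference that runs through month 6, when both arms have been treated. The three sections therefore describe different quantities for the same outcome.

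The coefficient named as the primary test can be zero, or carry the wrong sign, when P3 works. The authors also intend to use the pilot's effect sizes to plan a larger trial, so a coefficient that does not measure P3 against no P3 could mislead that planning.

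**Working it through.** **Inputs from the protocol article.** 30 couples per arm, 0.75 SD, α = .05 (taken as two-sided), visits at 0, 3 and 6 months, delayed arm on P3 from month 3.

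**Assumptions, not in the document.** Correlation over time ρ = 0.3, 0.5 or 0.7; complete data; SD 1 at each visit. The ratio of the immediate arm's month-6 effect to its month-3 effect is written k.

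**1. The plan's own figure.** For two means, the noncentrality is 0.75 × √(30/2) = 2.905. Power is 81.5% by the t test and 82.8% by the normal approximation. The stated 80% reproduces, but for a difference in means at one time, not for a slope difference.

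**2. What the slope coefficient weighs.** The generalised least-squares slope at 0, 3 and 6 months has weights (−1/6, 0, +1/6) under compound symmetry and under AR(1), at every ρ tried. The slope is (month 6 − baseline)/6 per month, and month 3 contributes nothing.

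**3. Value of the tested coefficient.** Let P3 add d in the first three months of access in either arm, as the pooling under Aim 3 presumes. Mean changes are (0, d, kd) in the immediate arm and (0, 0, d) in the delayed arm. A time trend common to both arms cancels. The slope difference is (kd − d)/6 = (k − 1)d/6 per month.

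**4. Rejection rates at d = 0.75.** Under compound symmetry, the standard error is √(2(1 − ρ))/6 × √(2/30), which is 0.0509, 0.0430 and 0.0333 at ρ = 0.3, 0.5 and 0.7.

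| k | Slope difference per month | ρ = 0.3 | ρ = 0.5 | ρ = 0.7 |
|---|---|---|---|---|
| 0.5 (halves) | −0.0625 | 23% | 31% | 47% |
| 1 (lasts) | 0 | 5% | 5% | 5% |
| 1.5 | +0.0625 | 23% | 31% | 47% |
| 2 (doubles) | +0.125 | 69% | 83% | 96% |

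Example, k = 0.5 and ρ = 0.5: −0.0625/0.0430 = −1.45, and Φ(1.45 − 1.96) is about 31%, with the sign favouring the delayed arm. Under AR(1), the k = 0.5 figures are 19%, 22% and 30%; k = 1 stays at 5%. A simulation of 400 trials at k = 1 and ρ = 0.5, fitted with a random-intercept model, gave a mean slope difference of 0.0016 per month and 5.0% rejection.

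**5. Would nonlinear time help?** With three visits, categorical time is saturated. For k = 1, the 2-df arm-by-time test has noncentrality 5.625/(1 − ρ) under compound symmetry: 8.04, 11.25 and 18.75. Power is about 71%, 85% and 98%. Such a test would detect the pattern, but it is not the stated test and it does not isolate the month-3 difference.

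**6. The month-3 arm contrast.** Its expected value is the full 0.75 SD.
- Month-3 means without baseline: 81.5%, as in step 1.
- Change from baseline to month 3: 67.5%, 81.5% and 95.8% at ρ = 0.3, 0.5 and 0.7.
- Baseline-adjusted: 0.75/√(1 − ρ²) × √15 = 3.05, 3.35 and 4.07, so Φ(that − 1.96) is about 86%, 92% and 98%.

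**The case against.** **The right comparison is already in the article.** The Aim 3 section promises it for outcomes A to D, and Randomization gives the same rationale. This stands. A reader might infer that an effective P3 would simply be reported as having no effect; the article does not support that, because the month-3 comparison, the pooled three-month change and the within-arm changes are also planned. The fault is that the named hypothesis test for C does not match them.

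**The coefficient need not be zero.** A reader might infer that it is about zero whenever P3 works. That needs an equal three-month gain in both arms and a plateau in the immediate arm. The pooling presumes the first; nothing states the second, and the article plans to look at effects after six months of use. This also stands. With continued growth the test can have power, but for duration of access.

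**Nonlinear time is allowed.** It would be wrong to say that it cannot help, as step 5 shows. But it is conditional on fit statistics, and the hypothesis is still worded as one slope coefficient. In addition, the average of the two arms under a lasting effect is linear (0, d/2, d), so a check on the time main effect alone may not select curvature.

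**It is a pilot, and the longitudinal work is introduced as exploring change.** True, and the article says that it is powered only for large effects. The slope test nevertheless sits under Primary Analyses and is called the primary hypothesis. The chi-square analysis there covers A, B and D only, and the t tests serve to characterise the sample.

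**Conclusion.** The point holds as a conflict between sections and a badly fixed test, for outcome C only. The stated slope difference does not measure P3 against no P3. Under an equal and lasting effect it is exactly 0, with 5% rejection at any correlation; this result needs complete, equally spaced visits and a linear time term. Under a halving effect in the immediate arm, the test rejects in about 23% to 47% of trials in favour of the delayed arm (compound symmetry, ρ 0.3 to 0.7; 19% to 30% under AR(1)). The correlations, the halving and the doubling are assumptions.

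The stated 80% power is not itself wrong: it is correct for a difference in means, and setting it against 5% compares two different tests. The calculations use the planned 30 couples per arm. The article reports 74 couples enrolled, but a larger sample does not move a coefficient whose expected value is zero.

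**What to change.** Reconcile the Primary Analyses section with the Aim 3 section:

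- For outcome C, enter time as a categorical factor and name the arm contrast at month 3 as the single primary test, two-sided at .05, preferably adjusted for baseline.
- Drop the slope difference as the primary hypothesis.
- Use month 6 only for change within arms and for questions about length of access, and label it so.
- State in the power section that the 0.75 SD refers to the month-3 contrast.

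The choice of baseline-adjustment method can be left to the analysis plan. The cost is a wording change and one contrast statement in the mixed-model code, with no new data. Because the Results section says that data are already being analysed, the change should be dated and disclosed.

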#### Intention to Treat

An intention to treat approach [55-57] will be used to include all enrolled participants in the analysis. Any individuals or couples lost to follow-up will be assigned an adverse outcome (for outcomes A, B, and D) to be able to include them in the analysis. For outcome C, those lost to follow-up will have to be excluded as the outcome is continuous and there is no cutoff to determine an adverse outcome. This follows an intention-to-treat analysis plan where all randomized individuals are included in the final analysis independent of their participation after baseline assessment, which will also help ensure that the benefit of randomization to balance confounders is retained.

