#### Primary Analyses

For outcomes A to D, descriptive statistics will be used to characterize the sample at each time point during the trial (baseline, month 3, and month 6), and by trial arm and couples’ HIV serostatus. Descriptive statistics will also be used to summarize cohort characteristics, relationship functioning variables, and sexual behaviors by the trial arm and by couples’ HIV serostatus. For couples, dyadic data will be calculated if there are no missing values from either partner. For continuous variables, couple-level mean variables will be generated by taking the averaged value from both partners’ scores. For within-dyad variables, couple-level differences will be generated by taking the absolute difference between each of the partner’s scores. Categorical dyadic variables will be generated based on whether both partners had the same or different answers. Two-sample 2-tailed *t* tests and chi-square tests will be used to evaluate differences between the immediate intervention arm and delayed intervention control arm for couple-level continuous and categorical independent variables, respectively, to further characterize the sample of couples in the trial.

An intention-to-treat (full analysis) approach will be used to determine the comparison between groups based on the initial randomization and using outcomes for all randomized individuals. The primary analysis will be to compare the proportions of couples with outcomes A, B, and D in the immediate intervention versus the proportions of couples with similar outcomes in the delayed control arm using a chi-square test with one degree of freedom in a univariate analysis from the corresponding contingency table. The efficacy rate will also be presented as the ratio between binomial proportions with CIs estimated through conventional methods used for the couple-level measurement.

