#### Relationship Dissolution

The approximate date and primary reasons for the relationship ending, including whether the reasoning is linked to study participation or intervention use, will be captured through the quantitative follow-up assessment or when the research staff contact participants, each month, to ensure that their contact information is current. To avoid intervention contamination and outcomes, couples who break up (ie, whose relationship has ended) during the pilot RCT will not be permitted to rejoin the study with a new partner. After completion of the pilot RCT, we will conduct a sensitivity analysis to quantitatively explore whether couples who break up comparatively differ from those who did not break up during the pilot RCT. Partners or couples’ data will still be used in the intention-to-treat analysis plan via the last observation carried forward method [55,57]. On the basis of the principal investigator’s prior intervention work with couples, we do not anticipate >5% of couples breaking up during the pilot trial. In the study by Mitchell [8] and another study involving couples [58], <5% of couples had ended their relationship while in the study, and none had reported their reasons as being associated with the study participation. In addition, the length of time that couples will wait before receiving the intervention is 3 months, which may further decrease the possibility of their relationship ending before receiving the intervention. For the reasons mentioned, we expect that the impact of couple dissolution will be minimal in creating systematically different samples between trial arms. However, we cannot predict the rate of relationship dissolution and will adjust analyses accordingly to account for any differences between trial arms and differences over time if observed.

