#### Missing Data

Reminders and incentives will be used to maximize participation in the follow-ups. For the primary outcome measures, any missing data due to attrition would be handled as mentioned in the Intention to Treat section. In addition, missing data mechanisms [61-63] will be examined by comparing differences between the dropouts and the observed data. We will perform 25 conditional model-based multiple imputations within group using SAS PROC MI, and will aggregate the results into an overall group, time, and group-by-time interaction with SAS PROC MIANALYZE to provide unbiased intervention effects and their variances. This will also be advantageous if there is a differential dropout for the delayed condition due to wait time. To ensure the validity of the imputed data, 4 parallel models will be performed as a sensitivity analysis on (1) imputed data, (2) completers-only data, (3) assuming adverse outcome for those missing, and (4) applying GLMMs that have the advantage of handling incomplete unbalanced repeated-measures data by incorporating population average and subject-level trajectories, and in turn providing unbiased estimates of parameter of interests. If necessary, post hoc power analyses will be performed using the bootstrap method to calculate the observed power for the detected effect size.

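### The rules for break-ups, outcome C dropouts and losses on A, B and D conflict, and scoring losses as adverse favours whichever arm loses fewer couples

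*Protocol article*

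**What the plan says.** Four parts of the protocol article bear on this.

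- **Analytic Plan, Intention to Treat.** "Any individuals or couples lost to follow-up will be assigned an adverse outcome (for outcomes A, B, and D"). For outcome C, "those lost to follow-up will have to be excluded as the outcome is continuous" and has no cutoff that would define an adverse value. The same paragraph says that everyone randomized is in the final analysis.
- **Relationship Dissolution.** The earlier section of this name (before Incentives) removes couples who report a break-up, after one further assessment where the break-up falls between visits. The later one, in the Analytic Plan, says that their "data will still be used in the intention-to-treat analysis plan via the last observation carried forward method". It does not limit this to particular outcomes.
- **Missing Data.** Attrition on the primary outcomes follows the Intention to Treat section, so missing = adverse is the primary rule for A, B and D. The section then plans 25 multiple imputations within arm and says of them: "This will also be advantageous if there is a differential dropout for the delayed condition due to wait time". Four parallel sensitivity analyses follow: imputed data, completers only, missing = adverse again, and "applying GLMMs that have the advantage of handling incomplete unbalanced repeated-measures data".
- **Primary Analyses.** A, B and D are compared between arms as proportions of couples, "using a chi-square test with one degree of freedom in a univariate analysis from the corresponding contingency table". Outcome C is fitted with a mixed model over baseline, month 3 and month 6.

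**The concern.** A couple that breaks up and is removed has no later visits. Read literally, it is lost to follow-up and scored adverse on A, B and D, and it is also a break-up whose last value is carried forward. The two rules can give opposite values, and no order of precedence is stated. HIV and STI tests are done only at baseline and month 6, so LOCF could turn a baseline infection result into the month-6 outcome.

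For outcome C, the reason given for exclusion does not apply to the model that is planned, and the exclusion contradicts the statement that all randomized participants are analysed.

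For A, B and D, missing = adverse is often thought conservative. It is not conservative for a comparison: it adds failures to each arm in proportion to its losses, so unequal losses create a difference where none exists. The pilot is meant to supply effect sizes for a later trial, so a distorted ratio matters even if it is not significant.

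**Working it through.** **Inputs from the article**
- Planned size: "60 couples randomized to 2 arms (30 couples in each"), allocated 1:1.
- Test level: "For all analyses, the α level was set at .05 with 95% CI".
- Reported retention at month 6: 68/74 = 91.9%, so 6 couples lost. Losses by arm and losses at month 3 are not given.
- Expected break-ups: at most 5%, that is 0.05 × 60 = 3 couples.

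**Assumptions (not in the article)**
- 37 couples per arm.
- The split of the 6 losses, the true rates, and no true effect.
- Losses unrelated to outcome.

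**1. The plan's own power figures.** With 30 couples per arm, a two-sample t test has 81.5% power for 0.75 SD. For a 35-point difference, the chi-square test has 79.7% power at the least favourable rates (32.5% vs 67.5%). Both agree with the stated 80%, and this point does not affect them. The power for D cannot be reproduced because no base rate is given.

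**2. Break-ups.** One couple scored one way rather than the other moves an arm of 30 by 1/30 = 3.3 points. If all 3 expected break-ups fell in one arm, that would be 10 points.

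**3. Outcome C.** The Primary Analyses model is a mixed model on three visits. A couple seen at baseline and month 3 but not at month 6 contributes two visits, and no cutoff is needed. The Missing Data section credits these models with exactly this property. Excluding such a couple is therefore neither required nor consistent with the rest of the plan.

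**4. Missing = adverse.** With L couples lost of 37 in an arm:
- D component with true risk q: analysed risk = (L + (37 − L)q)/37
- A or B with true success p: analysed success = (37 − L)p/37

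| Outcome, true rate in both arms | Losses, immediate:delayed | Immediate | Delayed | Ratio |
|---|---|---|---|---|
| D, 10% | 3:3 | 6.4/37 = 17.3% | 6.4/37 = 17.3% | 1.00 |
| D, 10% | 2:4 | 5.5/37 = 14.9% | 7.3/37 = 19.7% | 0.75 |
| D, 10% | 1:5 | 4.6/37 = 12.4% | 8.2/37 = 22.2% | 0.56 |
| D, 5% | 1:5 | 2.8/37 = 7.6% | 6.6/37 = 17.8% | 0.42 |
| D, 20% | 1:5 | 8.2/37 = 22.2% | 11.4/37 = 30.8% | 0.72 |
| D, 60% (for example condomless anal sex) | 1:5 | 22.6/37 = 61.1% | 24.2/37 = 65.4% | 0.93 |
| A or B, 40% success | 1:5 | 14.4/37 = 38.9% | 12.8/37 = 34.6% | 1.125 |

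A 5:1 split inverts each ratio.

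Exact enumeration of the chi-square test, with these losses held fixed and no true effect, gives these rejection rates:
- D at 10%: 3.0% for 2:4 and 14.0% for 1:5.
- A or B at 40%: 5.8% for 1:5.

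If the 6 losses fell at random over 37 and 37, the chance of 5 or more in the delayed arm is about 10%.

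Equal losses create no false difference, but they do cost power. With 8% lost in each arm of 30 and true rates of 65% vs 30%, power is 72.1% under missing = adverse, about 75.4% for completers, and 79.0% with no loss.

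**5. LOCF and the outcome C exclusion.** The direction of any bias depends on who leaves and on their last values. The article gives neither, so none can be derived.

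**The case against.** The strongest reply has five parts.

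- **Delayed-arm dropout.** A reader might infer that the plan expects more dropout in the delayed arm, so that its rules as a whole tilt toward P3. The article does not support that. The Missing Data sentence is conditional and gives no rate. On break-ups, the Relationship Dissolution section expects minimal difference between arms and promises adjustment if one appears. Only missing = adverse has a derivable direction, and reversing the split reverses it. This objection stands.
- **Size.** The 1:5 split is one scenario among several. For A and B it produces 4.3 points, against the 35 points the trial is powered for. The 6 losses are month-6 losses, whereas the Aim 3 section places the between-arm comparison at baseline to month 3, so they bear less certainly on A and B. Outcome D also includes condomless anal sex, and having had it with the partner is an entry criterion; for so common a component the distortion is small. This also stands.
- **Safeguards.** The four parallel analyses would expose a result driven by dropout. True, but the primary result would still be the one most exposed to unequal losses.
- **Break-ups.** These could be read as a specific case governed by a specific rule, affecting 5% of couples or fewer. That reading is possible, but the article does not state it, and it leaves the carried-forward baseline infection result in place.
- **Timing.** Data collection has ended and staff know the allocation, so a change now is not wording alone. This stands and shapes the fix.

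None of this rescues the reason given for excluding outcome C dropouts.

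**Conclusion.** The concern holds as a conflict among the missing-data rules and a poor choice of primary rule. The outcome C exclusion is wrong as written, and the break-up rule is unresolved; both follow from the text without any assumption.

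The bias from missing = adverse is conditional. It is zero with equal losses. It favours P3 only if the delayed arm loses more, and the control arm if the reverse holds. Under the assumptions of 37 per arm, no true effect and losses unrelated to outcome, its size at the reported total loss runs from none (3:3) to a risk ratio of about 0.56 for a 10% D component (1:5). It stays modest for a common D component (0.93) and for A or B (1.13). The documents do not support saying that dropout has produced, or will produce, a false effect.

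This should be fixed. In a pilot with 92% retention, and with imputation already planned, it does not undermine the trial.

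**What to change.** 1. **Outcome C:** analyse all available visits in the planned mixed model and delete the exclusion.
2. **Break-ups:** state one rule for all outcomes. Use the couple's final assessment when it falls at the visit being analysed; otherwise treat the value as missing like any other. Delete LOCF.
3. **A, B and D:** make the planned 25 within-arm multiple imputations primary, with a simple imputation model for rare D events. Keep missing = adverse and completers-only as sensitivity analyses.
4. **Losses:** report them by arm and visit, so that readers can judge how far missing = adverse could have moved each comparison.
5. **Record:** because collection has ended, make this a dated amendment before by-arm results are reviewed. If they have already been seen, report the new analysis as post hoc beside the rule now written.

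The cost is small: no new data, and the methods are already in the Missing Data section. The downside is reliance on missing at random, and on few events when imputing rare D components. The retained sensitivity analyses give a check on this.
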